## Abstract

**Introduction:**

The WHO recommends antenatal calcium supplementation (1500–2000 mg/day) to prevent pre-eclampsia in settings with low dietary calcium intake. Implementation is limited partly due to the need for three daily doses, although a lower 500 mg dose may be non-inferior. Current guidelines also recommend separating calcium from iron-containing supplements because concurrent intake may inhibit iron absorption. This individually randomised, controlled, non-inferiority trial will test whether co-administration of calcium and multiple micronutrient supplement (MMS) (CaMMS) is non-inferior to separate administration for haematological and iron status.

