The current formulation of MMS does not contain calcium. Low dietary calcium intake is associated with hypertensive disorders of pregnancy and preeclampsia,^14^ which causes 40 000 maternal deaths annually worldwide.^15^ A 2018 Cochrane meta-analysis of 27 calcium trials^16^ showed that calcium in doses ≥1 g for women with low dietary calcium intake reduced high blood pressure by 35%, preeclampsia by more than half and death or serious morbidity by 20%. The Cochrane review also reported that daily doses of ≥1 g also reduced preterm birth by 24% but had no effect on SGA. In addition to IFA or MMS, WHO recommends that women with low-calcium diets receive 1.5–2.0 g daily in divided doses of 500 mg.^17^ This recommendation has not been widely implemented,^18^ likely due to the cost of supplements and adherence challenges with divided doses. A recently completed non-inferiority (NI) trial carried out in India and Tanzania indicated that a daily 500 mg dose is non-inferior to the higher dose in preventing preeclampsia.^19^ Results from the site in India also suggested that it was non-inferior for the preterm birth outcome.^19^

Given the new evidence that a 500 mg calcium dose is non-inferior to 1500 mg for key public health outcomes,^19^ there is increasing interest in modifying the MMS formulation to include 500 mg elemental calcium. A remaining challenge is that WHO recommends that calcium supplements be taken separately from iron-containing supplements because concurrent ingestion may reduce iron absorption.^17^ However, this supposition was largely based on evidence from studies of iron absorption from single test meals or short-term bioavailability.^20–25^ A 2021 meta-analysis found that, while there was a significant association between the use of calcium supplements and lower serum ferritin concentration, this did not translate into a difference in haemoglobin (Hb) concentration.^26^ It is important to note that most studies had specifically excluded pregnant women and were primarily carried out in high-income country settings, where baseline iron status was likely higher.^26^

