## Methods and analysis

### Study design

This is an NI trial designed to assess the impact of UNIMMAP MMS and Ca (500 mg) taken concurrently, relative to taking them separately, on haematological and iron status of women and infants. Women will be individually randomised in a 1:1 ratio to take both supplements in the morning (‘together’) or to take the MMS in the morning and the calcium in the evening (‘separate’). Counselling messages and supplement packaging will not enable blinding of participants or study staff with direct participant contact. However, laboratory staff measuring the trial’s outcomes and investigators not directly involved in field work will be blinded. The code will be broken when all outcomes have been assessed. Enrolment commenced in Pakistan on 25 August 2025 and in Burkina Faso on 12 September 2025. Assuming an 8-month recruitment period for Burkina Faso and a 12-month period for Pakistan, we anticipate that field work will be completed by May 2027.

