### Outcomes

Our primary aim is to evaluate the effect of co-administered Ca and MMS on mean Hb concentration at 30<34 weeks of gestation, as measured by complete blood count (CBC).

Our secondary aims are to evaluate the effect of co-administered Ca and MMS on:

Iron status of pregnant women at 30<34 weeks of gestation (see table 1 for justifications): ferritin, soluble transferrin receptor (sTfR), hepcidin and erythropoietin (EPO) concentrations, as well as sTfR-ferritin index and hepcidin-EPO ratio; ferritin and sTfR will be presented with and without adjustment for inflammation.^34^Haematological status of pregnant women at 30<34 weeks of gestation: red blood cell count, mean corpuscular volume, mean corpuscular Hb and mean corpuscular Hb concentration.Hb concentration of infants within 72 hours of birth.Iron status of infants within 72 hours of birth.

**Table 1 T1:** Secondary iron status outcomes to be used in the CaMMS Trial

Outcome	Justification
Ferritin	Measure of storage iron; as inflammation increases ferritin and can mask true iron deficiency, data will be presented as unadjusted and adjusted using the BRINDA method^34^: Ferritin_adjusted_=ferritin_unadjusted_ – β_1_(CRP_obs_ – CRP_ref_) – β_2_(AGP_obs_ – AGP_ref_) – β_3_(malaria)
Soluble transferrin receptor (sTfR)	Measure of tissue iron demand for erythropoiesis; data will be presented both unadjusted and adjusted for inflammation: sTfR_adjusted_=sTfR_unadjusted_ – β_1_(CRP_obs_ – CRP_ref_) – β_2_(AGP_obs_ – AGP_ref_) – β_3_(malaria)
sTfR:log-ferritin ratio	Expressed to distinguish iron deficiency from apparent deficiency that occurs with inflammation; basis for calculation of total body iron stores
Hepcidin	Regulator of iron absorption; iron sufficiency and inflammation result in increased hepcidin and decreased iron absorption
Erythropoietin (EPO)	Endocrine signal for erythrocyte production
Hepcidin:EPO ratio	More sensitive measure of poor iron status, combining information regarding absorbed and circulating iron with extent of hypoxia

CaMMS, calcium and multiple micronutrient supplement; CRP, C-reactive protein.

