Exploratory outcomes, defined as pre-specified outcomes not included in the confirmatory analysis and for which the trial was not powered to detect differences, include anaemia (Hb<110 g/L) at 30<34 weeks and, as an indicator of intervention safety, severe anaemia (Hb<70 g/L) at 20<24 weeks and 30<34 weeks of gestation. Other exploratory outcomes, defined in table 2, include iron deficiency, iron deficient erythropoiesis, iron deficiency anaemia, birth weight, LBW, gestational age at birth, weight-for-gestational age (GA) Z-score, small-for-gestational age, miscarriage and stillbirth.

**Table 2 T2:** Definitions of exploratory outcomes to be assessed in the CaMMS trial

Exploratory outcomes	Definition
Anaemia	Hb<110 g/L at 30<34 weeks of gestation
Intervention safety	Severe anaemia (Hb<70 g/L) at 20<24 weeks or 30<34 weeks
Iron deficiency	Plasma ferritin<15 µg/L at 30<34 weeks of gestation^*^
Iron-deficient erythropoiesis	sTfR concentration>8.3 mg/L at 30<34 weeks of gestation
Iron deficiency anaemia	Concurrent anaemia (Hb<110 g/L) and iron deficiency (plasma ferritin<15 µg/L)^1^ at 30<34 weeks of gestation
Birth weight	Infant weight within 72 hours of birth
Low birth weight	Infant weight<2500 g within 72 hours of birth
Gestational age (GA) at birth	GA at birth in weeks based on screening ultrasound and INTERGROWTH-21st standard
Preterm birth	GA at birth<37 weeks of gestation
Weight-for-gestational age Z-score	Calculated based on weight≤72 hour of birth using the INTERGROWTH-21st standard
Small-for-gestational age	<10th percentile of weight-for-gestational age using INTERGROWTH-21st standard
Miscarriage	Foetal loss <20 gestational weeks
Stillbirth	Foetal loss ≥20 gestational weeks

* An alternative physiologically based ferritin threshold of 25 µg/L will be used in sensitivity analyses based on recent evidence that this higher threshold may better identify individuals at an earlier stage of iron deficiency, when iron stores are insufficient for red blood cell production and other tissue functions.

CaMMS, calcium and multiple micronutrient supplement; Hb, haemoglobin ; sTfR, soluble transferrin receptor.

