**Figure 3 F3:**
[figure not shown]
Interpretation of noninferiority results from CIs using the fixed margins method. MMS, multiple micronutrient supplement.

If <10% of outcomes are missing due to losses to follow-up, specimen handling or testing considerations, or very preterm or extremely preterm birth prior to 30 weeks, we will perform multiple imputation by chained equations of missing outcome data using predictive mean matching to generate 50 complete datasets for ITT analysis.^46^ Multiple imputation has been proposed as a robust strategy to address outcome missingness in NI trials under the assumption that data are missing at random.^47^ Our imputation model will include, at minimum, treatment arm and covariates we have prespecified for inclusion in adjusted models. Multiple imputation will be performed within country to preserve site-specific data structures. Analyses will be repeated on each imputed complete dataset, and results will be pooled using Rubin’s method. We will conduct sensitivity analyses using inverse probability weighting to assess the robustness of conclusions to missingness if ≥10% of outcome data are missing.^48^

The analytic approach for secondary (table 1) and exploratory outcomes (table 2) will use ITT, PP and mITT to determine superiority of Ca and MMS taken together compared with Ca and MMS taken separately. We will use the same two-stage approach to analyse the countries separately and then pool country-specific treatment effects. For ferritin and soluble transferrin receptor, we will present results both unadjusted and adjusted for inflammation (CRP and AGP) using the methods published by Namaste *et al.*^34^ For binary outcomes, we will use log-binomial regression models with a log link and a binomial response distribution to estimate prevalence ratios with 95% CIs. P values will be adjusted for multiple comparisons using the Holm method, and statistical significance will be determined at α=0.05.

A full Statistical Analysis Plan is available at https://doi.org/10.17605/OSF.IO/36W58.

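### Non-inferiority is announced for iron status, but only haemoglobin has a margin; iron markers get Holm-adjusted superiority tests that cannot support that claim

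*Protocol article*

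**What the plan says.** - **Objective.** The Abstract (Introduction) states that the trial will test whether co-administration "is non-inferior to separate administration for haematological and iron status". Study design calls it a non-inferiority trial of the effect of taking the supplements concurrently, "relative to taking them separately, on haematological and iron status of women and infants".
- **Margin and rule.** The Abstract (Methods and analysis), Sample size and Statistical methods give one margin, −3 g/L, and apply it to haemoglobin only.
- **Iron-status outcomes.** Outcomes lists six maternal iron indices as secondary: "ferritin, soluble transferrin receptor (sTfR), hepcidin and erythropoietin (EPO) concentrations, as well as sTfR-ferritin index and hepcidin-EPO ratio".
- **Test for these outcomes.** Statistical methods says the secondary (Table 1) and exploratory (Table 2) analyses "will use ITT, PP and mITT to determine superiority of Ca and MMS taken together compared with Ca and MMS taken separately". It adds: "P values will be adjusted for multiple comparisons using the Holm method, and statistical significance will be determined at α=0.05".
- **Direction of the worry.** The Introduction reports WHO advice that "calcium supplements be taken separately from iron-containing supplements because concurrent ingestion may reduce iron absorption". It also cites a meta-analysis in which "there was a significant association between the use of calcium supplements and lower serum ferritin concentration", without a corresponding haemoglobin difference.
- **Safety indicator.** Outcomes places among the exploratory outcomes, "as an indicator of intervention safety, severe anaemia (Hb<70 g/L) at 20<24 weeks and 30<34 weeks of gestation".

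**The concern.** The announced objective and the planned hypothesis do not match. A non-inferiority conclusion needs a margin and a confidence limit compared with it. For iron status the article gives neither, and names superiority of the arm whose possible harm is the question. Failing to show that co-administration improves ferritin says nothing about whether it lowers ferritin.

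The mismatch sits where it matters. On the protocol's own account of earlier evidence, ferritin can be lower while haemoglobin is unchanged, so the haemoglobin endpoint could pass while iron status has fallen.

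Holm adds to this. Adjustment for multiplicity guards against false claims of benefit. Where the reassuring result is the absence of a significant difference, a stricter threshold makes reassurance easier to obtain. As worded, the adjustment is not limited to benefit and could reach the final p value for severe anaemia.

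**Working it through.** **1. The plan's own sample size.** Inputs from Sample size: margin 3 g/L, SD 17 g/L, one-sided α 0.025, power 90%, loss 15%.

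n per arm = 2 × 17² × (1.960 + 1.282)² / 3² ≈ 675. Inflated: 675 / 0.85 ≈ 795 per arm, or 1590 per country. This reproduces the stated 1600 per country. Analysed women per arm per country: 800 × 0.85 = 680.

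**2. Number of tests.** The Holm family is not stated. Three readings:
- 6: the rows of Table 1, which Statistical methods ties to the secondary outcomes.
- 12: all secondary aims in Outcomes (6 iron indices, 4 red-cell indices, infant haemoglobin, infant iron status).
- 25: those 12 plus the 13 rows of Table 2.

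**3. Power to declare a true fall in ferritin, one country.** Assumptions not in the document: ferritin analysed on the log scale, SD of ln ferritin 0.6 to 0.9, a true 10% fall in geometric mean, two-sided test.

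z = −ln(0.9) / (s × √(2/680)); power = Φ(z − z_crit), with z_crit at two-sided 0.05/m. The critical values are 1.960 (m = 1), 2.638 (m = 6), 2.865 (m = 12) and 3.090 (m = 25).

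For s = 0.7: z = 0.1054 / 0.0380 = 2.775. Unadjusted: Φ(0.815) = 79%. First Holm step with m = 6: Φ(0.137) = 55%.

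| SD of ln ferritin | Unadjusted | m = 6 | m = 12 | m = 25 |
|---|---|---|---|---|
| 0.6 | 90% | 73% | 65% | 56% |
| 0.7 | 79% | 55% | 46% | 38% |
| 0.9 | 58% | 32% | 24% | 18% |

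The Holm columns are lower bounds. The first-step threshold binds only if no other marker in the family has already been rejected. Power under Holm therefore lies between the relevant column and the unadjusted one.

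**4. Pooled estimate.** The plan also pools the countries. With 2 × 680 = 1360 per arm, a common 10% fall and a fixed-effect estimate, z is multiplied by √2. For s = 0.7, z = 3.925: power is 98% unadjusted and 90% at m = 6. At m = 6 it is 97% for s = 0.6 and 66% for s = 0.9.

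**5. Would a ferritin margin be feasible?** Take one-sided α 0.025, 680 per arm, no true difference, and power = Φ(−ln(margin) / (s × √(2/680)) − 1.960). Over s = 0.6 to 0.9, power is at least 99.5% for a ratio margin of 0.80, about 91% to 99.9% for 0.85, and 58% to 90% for 0.90. These margins are illustrations only. The document gives no ferritin effect from which to derive one.

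**The case against.** The strongest reply is that non-inferiority is confined to haemoglobin wherever it is made operational. Outcomes lists iron status as a secondary aim to evaluate an effect, and the strengths and limitations box admits that the trial is not powered for secondary outcomes such as iron deficiency. On this view one Abstract sentence and a similar phrase in Study design are loosely worded. That stands as to the simplest repair, but it leaves the published objective unmet by the planned analysis.

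Four stronger readings are tempting, and the document does not support them.

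- **A fall in ferritin could never be declared.** That would follow only if superiority meant a one-sided test. The stated α of 0.05 has no one-sided qualifier, whereas Sample size says one-sided explicitly for haemoglobin. The natural reading is two-sided. Country-specific effects with 95% CIs, then pooled estimates, are planned under the same two-stage approach.
- **Non-significance will be reported as no difference.** No section says so. It is a foreseeable misreading when no margin exists, not a stated rule.
- **Twenty-five tests share one Holm family.** Outcomes defines exploratory outcomes as outside the confirmatory analysis, which argues against pooling them with the secondary ones, and the unseen SAP may define the family. Iron markers are also likely to move together if absorption falls, which would relax Holm.
- **Holm governs safety monitoring.** Monitoring lets the DSMB consider severe anaemia quarterly at p<0.05, with no Holm adjustment mentioned. Only the final reported p value is in question.

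**Conclusion.** The point holds as an internal mismatch that does not depend on the unseen SAP: non-inferiority is announced for iron status, a margin exists only for haemoglobin, and iron markers are assigned Holm-adjusted superiority tests. Following the article as written cannot deliver the announced iron-status conclusion. The haemoglobin decision is untouched.

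The size of the Holm effect is illustrative. For a 10% fall and a log-SD of 0.7, the worst-case loss per country is from 79% to 55% power with six tests, and deeper only if the family is larger. The pooled estimate loses much less. The figures rest on the assumed log-SD and fall, and on a Holm family that the article does not define. They show that a real fall could be non-significant in one country, not that it would go undetected.

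**What to change.** 1. In the Abstract and Study design, confine the non-inferiority claim to haemoglobin. Alternatively, if the investigators can justify one, pre-set a margin for ferritin and judge the confidence interval against it. The margin is optional.
2. In Statistical methods, replace superiority for secondary and exploratory outcomes with two-sided estimation (differences or ratios) and unadjusted 95% CIs. State that a non-significant result is not evidence of no harm.
3. Limit Holm to claims of benefit and name its family. Leave severe anaemia outside it, in line with the DSMB's unadjusted review under Monitoring.

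The cost is wording in the protocol, and in the SAP if it says the same. Sample size and data collection do not change. The edits should be made before the allocation code is broken. The downside is that the iron-status conclusion may be less favourable than a statement of no significant difference.

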**Trial registration number:**

NCT06568315.

STRENGTHS and LIMITATIONS OF THIS STUDYThe calcium and multiple micronutrient supplement (CaMMS) non-inferiority trial testing the impact of co-administering calcium and MMS on haemoglobin and iron status will include sites in both Sub-Saharan Africa and South Asia, enhancing external validity and capturing diverse anaemia aetiologies and background calcium intakes that may influence the nutrient-nutrient interaction.The separate administration arm introduces greater complexity that could affect adherence; however, this is mitigated through intensive adherence promotion at monthly dispensing and household visits and further strengthened by unannounced mid-day household visits to assess real-world supplement consumption patterns despite the lack of direct observation.Although the trial is not powered for secondary outcomes such as anaemia, iron deficiency and pregnancy outcomes, it is adequately powered for the primary non-inferiority endpoint, which is the main objective informing policy-relevant conclusions.

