### Sample size

For this NI trial, we calculated an NI margin using guidelines developed by the US Food and Drug Administration and the European Medicines Agency.^35^ Briefly, the NI margin is based on effect sizes from prior meta-analyses or trials of the active control, with the smallest expected treatment effect (M1) set at the limit of the 95% CI that is closest to the null effect. We found no studies comparing the effects of MMS and calcium taken together versus placebo, and data comparing MMS to a placebo were similarly limited. We therefore used the pooled effect size for Hb concentration at or near term (8.88 g/L (95% CI 6.96 to 10.8)) from 20 trials of iron-containing supplements, compared with the same formulations without iron, no treatment or a placebo.^36^ As the lower limit is clinically large (7.0 g/L), common practice is to preserve 50% of the minimum effect for an NI margin (M2) of −3.5 g/L. However, the absolute value of this effect exceeds 3.0 g/L, which we would consider clinically meaningful based on the difference between the third and fifth normative centiles for maternal Hb at 30<34 weeks’ gestation derived from the INTERGROWTH-21st Project,^37^ that is, the difference between a probable diagnosis of being at high risk versus anaemic. Therefore, we selected a more conservative NI margin of −3.0 g/L.

We assumed a one-sided α=0.025; 90% power; an SD of 17 g/L, based on prior data from both sites and assuming equal group variance across treatment arms^38,39^; and 15% loss to follow-up. Accordingly, a sample of 1600 women per country (3200 women in total) will be required to conclude NI, in each country independently; that is, that the lower limit of the 95% CI around the difference in Hb concentration between the intervention (MMS and Ca taken together) versus control (MMS and Ca taken separately) is greater than −3 g/L.

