After administering the questionnaire, women will undergo a physical exam, where staff will measure women’s weight to the nearest 100 g using an ADE M316600 electronic floor scale (ADE Germany GmbH, Hamburg, Germany), height to the nearest 1 mm using an ADE MZ10042 mobile stadiometer (ADE Germany GmbH, Hamburg, Germany), mid-upper arm circumference to the nearest 1 mm, and blood pressure using the Microlife Cradle VSA (Microlife, Widnaw, Switzerland). They will then use antecubital venipuncture to collect a venous blood sample into (a) an untreated or serum-separator blood collection tube for serum-based analyses (ferritin; soluble transferrin receptor; hepcidin; erythropoietin; C-reactive protein (CRP); α_1_-acid glycoprotein (AGP)) and (b) an EDTA-treated evacuated blood collection tube for assays requiring whole blood (CBC; haemoglobinopathies; malaria parasitaemia in Pakistan). While the Hb measured by HemoCue at screening will serve as an initial screening for severe anaemia, results of the CBC will be used for the baseline Hb measurement. CBC results will be reviewed to identify any women with Hb<70 g/L who were not flagged by on-site HemoCue testing. For the baseline visit, these women will be contacted to provide a referral and will be treated as post-randomisation exclusions. Blood samples will be stored in insulated containers with cold packs prior to transit to local laboratories for processing. Finally, women will be given two boxes of study supplements (one 4-week supply and a 4-week buffer) and receive counselling, as described above.

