As treatment effects may vary between countries due to differences in the determinants of Hb concentration, we will use a two-stage approach to combine treatment effect estimates across countries. In the first stage, we will estimate country-specific treatment effects and 95% CIs using simple linear regression models with a dummy variable for allocation. We will treat these site-specific analyses as separate hypothesis tests and will not correct for multiple testing across site-specific analysis results. In the second stage, we will pool the country-specific effects. Since between-country heterogeneity in treatment effects cannot be estimated precisely with only two countries, we will present both fixed-effect and random-effects estimates across countries. The latter will be performed using the inverse variance approach with the between-country treatment effect variance estimated by the DerSimonian and Laird method. Country-specific results will be the primary basis for the NI decision; the pooled estimates are secondary summaries to present the range of plausible pooled effects without relying on an imprecise estimate of between-country heterogeneity or assuming a common effect across countries. In addition to the unadjusted analyses, we will conduct sensitivity analyses including the following baseline covariates: parity, body mass index, height and baseline values for Hb, ferritin, CRP and AGP. We will follow the same approach for the ITT, PP and mITT analyses. NI will be determined using the fixed-margin methods (figure 3). That is, if the lower limit of the 95% CI around the difference in Hb concentration between the intervention and control is greater than the NI margin of −3 g/L, the intervention will be deemed non-inferior. We will use both ITT and PP approaches. For NI trials, PP analysis provides a more conservative assessment; however, as differential adherence between arms is possible, PP analysis may introduce bias through differential post-randomisation selection based on adherence. Therefore, while both analyses will be examined for consistency, ITT will be considered primary. We will also explore effect modification based on receipt of any iron treatment, extracted from health cards, and dietary iron and calcium intakes. A *p* value<0.05 for the interaction term will be considered statistically significant.

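### Apart from ferritin, no maternal secondary outcome is stated to be adjusted for its own baseline value, although those values are scheduled to be measured: an avoidable loss of precision, not a bias

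*Protocol article*

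**What the plan says.** All of this is in the protocol article.

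- **Main model.** Statistical methods estimates country-specific effects "using simple linear regression models with a dummy variable for allocation". No baseline term is included.
- **Adjusted model.** The same section adds sensitivity analyses with a fixed list: "parity, body mass index, height and baseline values for Hb, ferritin, CRP and AGP". The only baseline blood values on it are Hb, ferritin, CRP and AGP.
- **Secondary outcomes.** Later in Statistical methods: "We will use the same two-stage approach to analyse the countries separately and then pool country-specific treatment effects". They are tested for superiority, with Holm-adjusted P values.
- **Which outcomes.** Outcomes lists six maternal iron measures at 30<34 weeks (ferritin, sTfR, hepcidin, EPO, the sTfR-ferritin index and the hepcidin-EPO ratio) and four red-cell measures (red cell count, MCV, MCH, MCHC).
- **Baseline data.** The Baseline section takes venous blood for "serum-based analyses (ferritin; soluble transferrin receptor; hepcidin; erythropoietin; C-reactive protein (CRP); α_1_-acid glycoprotein (AGP", and EDTA blood for the complete blood count. Biospecimen analysis and Table 3 confirm the draw in early, mid and late pregnancy.

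**The concern.** The covariate list suits haemoglobin, because it contains baseline Hb. For nine of the ten maternal secondary outcomes it does not contain the variable likely to predict the outcome best, namely the same marker at enrolment. Moving baseline Hb into the primary model would not change this.

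The iron markers matter for interpretation. The Introduction cites a meta-analysis in which calcium supplements were associated with lower ferritin but with no difference in Hb. An interaction could therefore show in iron status while the primary outcome is non-inferior. If the intervals on these markers are wider than they need be, a real difference is more likely to be reported as non-significant and read as reassurance.

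**Working it through.** **1. The plan's own sample size.** Inputs from Sample size: "We assumed a one-sided α=0.025; 90% power; an SD of 17 g/L"; "we selected a more conservative NI margin of" −3.0 g/L; "15% loss to follow-up". With a true difference of zero:

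n per arm = 2 × 17² × (1.960 + 1.282)² / 3² = 674.8, so 675. Per country this is 1350, and 1350 / 0.85 = 1589. The stated 1600 per country reproduces.

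Evaluable women per arm per country: 1600 × 0.85 / 2 = 680.

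**2. Outcomes with their own baseline in a stated model.** Six iron plus four red-cell measures make ten. Ferritin is on the sensitivity list (and counts only if that list extends to secondary outcomes). The other nine are on no list.

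**3. Precision against the main model.** Let ρ be the correlation between an outcome and its own baseline. The article gives no ρ, so 0.3, 0.5 and 0.7 are assumed. In SD units:

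SE = √[(2/n)(1 − ρ²)], power = Φ(0.15/SE − z)

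The 0.15 SD effect is also assumed. At the first Holm step of an assumed family of ten, two-sided α = 0.05/10 = 0.005 and z = 2.807. At an uncorrected 0.05, z = 1.960.

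| ρ | Variance cut | SE (n = 680) | Power, α 0.005 | Power, α 0.05 |
|---|---|---|---|---|
| 0 (as planned) | – | 0.0542 | 48% | 79% |
| 0.3 | 9% | 0.0517 | 54% | 83% |
| 0.5 | 25% | 0.0470 | 65% | 89% |
| 0.7 | 49% | 0.0387 | 86% | 97% |

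The article does not state the Holm family size. With six outcomes (α = 0.0083), power is 55% unadjusted and 71% at ρ = 0.5. With twelve (α = 0.0042) it is 46% and 63%.

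**4. Pooled stage.** Assume fixed-effect pooling of two equal countries with equal SDs, so n = 1360 per arm. Unadjusted SE = √(2/1360) = 0.0383 and power at α = 0.005 is about 86.5%. It becomes 90%, 96% and over 99% at ρ = 0.3, 0.5 and 0.7.

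**5. Precision against the sensitivity model.** Baseline Hb and ferritin already act as partial proxies there. Let p be the proxy's correlation with the outcome and c its correlation with the own baseline. Then R² = (ρ² + p² − 2ρpc)/(1 − c²), and the further variance cut is 1 − (1 − R²)/(1 − p²). All three values are assumed:

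- ρ 0.3, p 0.2, c 0.5: R² = 0.093; further cut 1 − 0.907/0.96 = 6%.
- ρ 0.5, p 0.3, c 0.5: R² = 0.253; further cut 1 − 0.747/0.91 = 18%.
- ρ 0.6, p 0.3, c 0.5: R² = 0.360; further cut 1 − 0.640/0.91 = 30%.

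**6. Is baseline a safe covariate?** By the order given in the Baseline section, blood is drawn after allocation but before supplements are handed out at that visit. The study supplements cannot have affected it.

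**The case against.** **The SAP is not shown, and the article is condensed.** The SAP may name outcome-specific baselines, and the sentence on secondary outcomes carries over the two-stage structure without repeating the allocation-only model. This limits the point to the analysis as the article states it. But the article does more than stay silent: it names a first-stage model and a covariate list, and it describes no other model for continuous outcomes.

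**Nothing is invalid.** This stands in full. An allocation-only comparison is unbiased under randomisation, and the non-inferiority decision on Hb is untouched.

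**A reader might infer that the article itself calls these comparisons under-powered.** The article says "Although the trial is not powered for secondary outcomes such as anaemia, iron deficiency and pregnancy outcomes", but its examples are not the continuous markers at issue. With 680 per arm, the unadjusted model detects 0.152 SD per country with 80% power at α = 0.05, and 0.198 SD at the first Holm step of ten.

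**A reader might also take 48% as the trial's power for these outcomes.** It is a per-country figure at the strictest Holm step. Later steps are looser, and the planned pooling starts at about 86.5%.

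**A reader might infer that baseline information is not used at all.** That goes too far. Baseline Hb and ferritin are partial proxies in the sensitivity model, ferritin is itself a component of the sTfR-ferritin index, and the imputation model's contents are given only as a minimum, so further baselines may be added.

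**The correlation may be modest.** Baseline falls anywhere from 6 to under 20 weeks and the outcome at 30 to under 34, a gap of roughly 10 to 28 weeks. One ρ is unlikely to fit every marker. This is why a range is shown.

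**Conclusion.** The point holds as an avoidable loss of efficiency in the analysis that the article states. Nine of the ten maternal secondary outcomes have no stated adjustment for their own baseline, and ferritin has it only in a sensitivity analysis.

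The size depends on ρ, which the documents do not give. If ρ is near 0.3 the gain is small; at 0.5 it equals a sample one third larger (1/0.75 = 1.33). The power figures further assume a 0.15 SD effect, 15% loss and a Holm family of ten; the pooled figures assume two equal countries. The benefit is largest for the country-specific results and smaller for the pooled ones. The documents do not support calling the planned analysis biased or wrong. The case for changing it is that the data are already scheduled and the change costs almost nothing.

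**What to change.** In the secondary-outcome paragraph of Statistical methods, state that each continuous maternal secondary outcome at 30<34 weeks, ferritin included, is analysed per country by ANCOVA with its own baseline value as covariate.

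- Use the same scale for baseline and outcome: logs for skewed markers, the baseline ratio for a ratio, the baseline index for a red-cell index.
- Give a simple rule that retains women with a missing baseline, such as mean imputation or a missing-value indicator.
- Add that baseline to the outcome's imputation model.
- Keep the allocation-only estimate as a supporting analysis.
- Align the SAP, or, if it already says this, align the article with it.

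Infant outcomes have no baseline and stay as planned.

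The cost is a few lines of text, with no new samples, visits or participants. The small downside is a covariate that differs by outcome. Field work is expected to run to May 2027 and the code is broken only once all outcomes are assessed, so the change can still be pre-specified.
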